#### ii) To adapt and translate the Problem Solving Therapy for Primary Care (PST-PC) treatment manual to the local rural situation in Mubende district.

Presentations at the plenary sessions will be audio recorded and transcribed. Flip chart records from the different groups will also be collected. The resultant qualitative data will be analysed using thematic analysis techniques [41] and used to improve the revised draft PST-PC training materials.

#### iii) To evaluate the acceptability, feasibility, and impact on mental health outcomes of the Ebola+D mental health intervention.

Serial focus group discussions with lay health workers (n = 11) and in-depth interviews with supervisors (n = 5) and clinicians (n = 5) will be held and the results will be used iteratively to improve the intervention. Data will be collected on the clinical process, including the engagement of patients, ease of implementing the decision support algorithm, barriers experienced in the delivery of the treatment and modifications made. Exit interviews will be held with a sample of both adherent (n = 8) and non-adherent (have dropped out of the intervention) (n = 8) respondents to describe their experiences and reasons for adherence or non-adherence. To assess effectiveness of the mental health intervention, study participants will be interviewed by trained psychiatric nurse research assistants who are not part in clinical care at baseline, 3-months and 12-months using structured standardized questionnaire (**Fig 2**).

**Fig 2 pone.0329591.g002:**
[figure not shown]
Schedule of study activities. M, month. The questionnaire will assess for: psychological distress, using the SRQ-20 scores [29], depression, using the Patient Health Questionnaire (PHQ-9) [42,43], generalized anxiety symptoms, using the Generalized Anxiety Disorder 7 (GAD-7) [44], alcohol abuse disorder, using the Alcohol Use Disorders Identification Test (AUDIT) [45], suicidality, using the suicidality module in the Diagnostic and Statistical Manual of Mental Disorders (DSM) based structured interview, the M.I.N.I. neuropsychiatric interview (MINI Plus) [46], post-traumatic stress disorder, using the PTSD Checklist for DSM-5 (PCL-5) [47], social support, using the Multidimensional Scale of Perceived Social Support (MSPSS) [48], and degree of disability, using the Sheehan Disability Scale (SDS) [49]. Participants’ engagement with PST will be assessed after each session by the lay health worker using Stahl and colleagues (2017) Interventionists’ Rating Scales of Participants’ Engagement in PST [50]. This instrument has three scales: participation scale (one item), understanding of materials scale (one item), and homework effort scale (one item). Each of these scales is rated on a Likert scale ranging from 1(none) to 6 (excellent). Carers’ (lay health workers, supervisors, mental health specialists) perceptions and satisfaction levels with integration efforts at their clinic will be assessed using a modified Staff Survey adapted from Ede and colleagues, 2015 [51]. Monthly Health Management Information Systems (HMIS) records on mental health diagnoses of each PHCF clinic will be collected. A summary of indicators that will be collected is indicated in Table 1.

**Table 1 pone.0329591.t001:** Summary of indicators that will be collected.

Outcome	Definition	Source of Data	Endpoints
Mental Health Outcomes	Psychological distress, by comparing mean SRQ-20 scores at baseline with scores at 3 and 12 months.	SRQ-20 scores [29]	3 months, 12 months
	Depression, by comparing mean PHQ-9 scores at baseline with scores at 3 and 12 months.	PHQ-9 scores [42,43]	3 months and 12 months
	Generalised anxiety, by comparing mean GAD-7 scores at baseline with scores at 3 and 12 months.	GAD-7 scores [44]	3 months and 12 months
	PTSD, by comparing mean PCL-5 scores at baseline with scores at 3 and 12 months.	PCL-5 scores [47]	3 months and 12 months
	Alcohol abuse disorder, by comparing AUDIT scores at baseline with scores at 3 and 12 months	AUDIT scores [45]	3 months and 12 months
	Suicidality, by comparing suicidality module of the M.I.N.I. neuropsychiatric interview (MINI Plus) scores at baseline with scores at 3 and 12 months	Suicidality module of the M.I.N.I. neuropsychiatric interview (MINI Plus) scores [46]	3 months and 12 months
Functioning and adjustment	Degree of functional impairment in the domains of: work/school, social life and home life or family responsibilities	Assessments using the Sheehan Disability Scale (SDS) [52]	3 months and 12 months
	Social support, by comparing the Multidimensional Scale of Perceived Social Support (MSPSS) scores at baseline with scores at 3 and 12 months	Multidimensional Scale of Perceived Social Support (MSPSS) scores [48]	3 months and 12 months
Fidelity of delivery of the intervention by lay health workers	Degree to which an intervention is implemented as described in the protocol.	Audio recording of lay health worker therapy sessions rated using a fidelity assessment scale	3 months during delivery of the therapy
Engagement with intervention by study participants	Participants’ engagement with PST, undertaken after each session, assessment done by lay health worker on three scales: participation scale (one item), understanding of materials scale (one item), and homework effort scale (one item). Each of these scales is rated on a Likert scale ranging from 1(none) to 6(excellent)	Stahl et al., (2017)’s Interventionists’ Rating Scales of Participants’ Engagement in PST [50]	During the administration of the therapy in first 3 months
Engagement with intervention by study participants	Proportion of persons with psychological distress who receive recommended number of treatment sessions	Study records of each patient	3 months
Carers’ perceptions and satisfaction levels with integration efforts at their PHCF	Lay health workers, supervisors, clinicians, mental health specialists’ perceptions and satisfaction levels with integration efforts at their clinic	Assessed using the modified Staff Survey adapted from Ede and colleagues (2015) [51]	3 months
Intermediate health system outcomes	Outcomes related to the uptake and referral at each step of Ebola+D intervention, e.g., proportion who are referred and who subsequently attend each step.	Screening and study logbooks	3 and 12 months
Uptake of mental health services	Number of patients at PHCF who are accessing mental health services	Monthly HMIS records of each participating public health care facility	12 months

Qualitative data will be analysed using thematic analysis techniques. A bottom-up inductive coding approach will be employed to allow codes, patterns and themes to emerge directly from the data. Two researchers will independently code the data. Inter-rater reliability – the extent to which different coders/analysts arrive at similar or consistent observations – will be assessed through regular data analysis team meetings. These meetings will be used to compare coding outputs of the two coders with a purpose of resolving potential discrepancies and generating consensus and refining the coding framework. Process indicators will be collected and analysed using descriptive statistics. Data collection and analysis will be undertaken iteratively and used to improve the intervention in 3 monthly cycles. Preliminary data on the effectiveness of the intervention will be obtained by comparing mean scores of the mental health outcomes at baseline with those at 3 months and 12 months.

Data will be collected electronically using REDCap, a secure, web-based application designed to support Good Clinical Practice (GCP)-compliant data capture. All data entered on REDCap will be transmitted via encrypted (HTTPS/SSL) connections to prevent interception during data transfer. The REDCap database will be hosted on secure servers at the MRC/UVRI & LSHTM Uganda Research Unit, protected by institutional firewalls and regular security monitoring.

Access to the REDCap database will be strictly restricted to authorized study personnel only, based on a role-based access control system. User accounts will require strong passwords and two-factor authentication will be enabled where possible. An audit trail will automatically log all user activities, including data entry, edits, and downloads, ensuring accountability and traceability.

To maintain confidentiality, all study data will be anonymized by assigning unique study IDs to participants at enrolment. Personally identifiable information (PII), such as names and contact details, will be stored separately from research data in password-protected files with restricted access. The linking log between PII and study IDs will be securely stored and accessible only to the Principal Investigator and the data manager. No PII will be included in exported datasets used for analysis.

The data manager to identify data that are missing, inconsistent, or out-of-range, will run internally developed Stata verification/cleaning do-files. The clinic team will perform clinical quality checks to identify potential errors not captured in the automated verification process.

Data will be checked for missingness and sparsity for all the variables. Demographic and psychosocial characteristics of the participants will be summarised using frequencies and percentages for categorical variables, means and medians will be used to summarise continuous variables depending on the nature of the distribution of different types of disorders. The chi-square test and Kruskal Wallis test will be used to assess associations between each of the different factors and the outcome for categorical and continuous variables, respectively. We will use a cut-off of P < 0.1 (2-tailed test) to identify factors for inclusion in the subsequent analysis. To assess the effect of identified social and psychological factors on Remission at 3 months, Relapse at 12 months and Recovery at 12 months, random effects logistic regression models will be fitted. Other factors to consider based on prior literature will include gender, education level, age, and baseline severity of the condition.

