**Fig 1 pone.0329591.g001:**
[figure not shown]
Ebola+D study flowchart.

Eligibility criteria for participating in this study: i) Community member of Mubende district staying within the catchment area of the PHCF; ii) 18 years and above, iv) able to communicate in either English or Luganda (local language spoken in the study region and the language into which the questionnaires will be translated), v) has a WHO SRQ-20 score of 6 and above.

Exclusion criteria: i) unable to engage with the research process for any reason that may include sensory impairment or cognitive impairment.

The study aims to enrol at least 100 respondents with psychological distress (SRQ-20 score ≥ 6) from each of the 11 participating PHCFs. Enrolled respondents will be provided with PST at bi-weekly sessions. Monthly assessments will be undertaken to monitor their level of psychological distress using the SRQ-20 until psychological distress scores have fallen to less than 6. A patient will be declared in remission if after completing their prescribed therapy (PST or medication) they remain symptom free (SRQ-20 scores of less than 6) on two occasions one month apart. A full complement of supporting and resource materials including clinic posters, health worker aide-memoire, and patient and care-giver resource materials will be developed and evaluated. The reporting of the trial will be in accordance with the SPIRIT guidelines for interventional trials [40] (S1 File).

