### Sample size and power calculations

The study will be longitudinal, with participants followed over a 12-month period. Psychological distress will be assessed using the SRQ-20, with a score of 6 or higher indicating distress. The primary outcome of interest will be remission of distress, defined as an SRQ-20 score below 6. All participants enrolled at baseline will have a level of distress. The intervention is hypothesised to reduce distress prevalence by at least 25%.

Given the longitudinal design and the use of clinic-based interventions, clustering effects will be accounted for by applying a design effect of 1.2, which reflects improved clustering control. Statistical parameters will include a confidence level of 95%. The total sample size will be fixed at 1,000 participants, requiring adjustments to the effective sample size to account for clustering.

The power calculation will be performed using a z-test for two proportions to compare the baseline and post-intervention prevalence of distress.

Using the assumed 25% absolute reduction in distress prevalence, the adjusted effective sample size of 1,000 participants, and a two-tailed significance level of 0.05, the estimated power of the study is calculated to be 94.5%.

Given the 12-month follow-up period and the community-based nature of the intervention, we anticipate an attrition rate of approximately 15%, based on evidence from similar longitudinal studies in rural Ugandan settings. Despite the anticipated attrition, the study will maintain the recruitment target at 1,000 participants, acknowledging that some loss to follow-up is expected. The analysis will account for missing data through multiple imputation techniques and sensitivity analyses to ensure that the study maintains sufficient power and validity to detect the hypothesized effect size.

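### Factors for the remission, relapse and recovery models are chosen by one-at-a-time P<0.1 tests on the data that then estimate their effects, so the retained results are over-optimistic

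*Protocol article*

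**What the plan says.** The rule is in the protocol article, under Data collection, management, and analyses, part iii). It runs in three stages.

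- Screening: "The chi-square test and Kruskal Wallis test will be used to assess associations between each of the different factors and the outcome", with chi-square for categorical factors and Kruskal-Wallis for continuous ones.
- Selection: "We will use a cut-off of P < 0.1 (2-tailed test) to identify factors for inclusion in the subsequent analysis".
- Estimation: for the social and psychological factors so identified, "random effects logistic regression models will be fitted". The outcomes are "Remission at 3 months, Relapse at 12 months and Recovery at 12 months".

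The paragraph then adds: "Other factors to consider based on prior literature will include gender, education level, age, and baseline severity of the condition". No correction for having selected the factors on the same data is described.

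On clustering, Sample size and power calculations says "clustering effects will be accounted for by applying a design effect of 1.2, which reflects improved clustering control" and "The total sample size will be fixed at 1,000 participants". Recruitment is "from each of the 11 participating PHCFs".

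**The concern.** The models are meant to show the effect of social and psychological factors on outcome, so the estimates and intervals will be read as explanatory. A factor that enters because its P value fell below 0.1 in these data has been chosen partly for its chance error. Its P value and interval in the final model are then calculated as if no choice had been made.

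Three things are at stake:

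- **Null factors that pass** look far more convincing than they should.
- **Weak real factors** are mostly discarded, and exaggerated when kept.
- **Confounders** whose association appears only after adjustment for others can be screened out, which leaves the remaining odds ratios biased.

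Baseline severity deserves particular care. Everyone enters with an SRQ-20 score of 6 or more, and remission means falling below 6. A participant who enters at 6 needs to lose 1 point (6 − 1 = 5); one who enters at 15 needs to lose 10 (15 − 10 = 5). Distance from the cut-off is therefore a likely strong determinant of remission. The depression, anxiety and PTSD scales probably correlate with it and could pass the screen as proxies. The wording does not commit the models to include it.

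**Working it through.** The plan gives no figure for this analysis. Its 94.5% power refers to the baseline versus post-intervention comparison and is not used here.

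**Inputs from the article.** Threshold 0.10; three binary outcomes; 1,000 participants; 11 facilities; design effect 1.2; attrition about 15%.

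**Assumptions.** 20 candidate factors (range 10 to 40), because the number is not stated. Facility is taken as the random effect: the level is not named, but each outcome is one value per participant.

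**1. Inference after the screen, by formula.** If a null factor has nearly the same test statistic in the screen and in the model:
- P(P<0.05 given P<0.1) = 0.05/0.10 = 50%.
- Coverage of its 95% interval = 1 − 0.50 = 50%.

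**2. The same by simulation.** 11 facilities × 77 participants (1,000 × 0.85 = 850; 850/11 ≈ 77), 400 runs, 20 null factors. Kruskal-Wallis screen at P<0.1, then a logistic model with facility intercepts (fixed intercepts standing in for random ones).

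| Outcome ICC | Factor ICC | Nulls passing | Of these, P<0.05 | Coverage of passing nulls |
|---|---|---|---|---|
| 0.0022 | 0 | 1.95 | 0.93 | 52% |
| 0.05 | 0 | 1.96 | 0.97 | 51% |
| 0.05 | 0.1 | 2.83 | 0.70 | 75% |

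In the first row, at least one null factor reached P<0.05 in 61% of runs. In the last row the screen and the model disagree more, so coverage is less poor but still well below 95%.

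**3. A weak true effect.** With log odds ratio 0.10 per SD (outcome ICC 0.0022), the factor passed in 40.5% of runs and was dropped in 59.5%. When kept, its mean estimate was 0.168, or 0.168/0.10 = 1.7 times the truth, and its interval coverage was 90%.

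**4. How many null factors pass.** Expected number = 0.1K; chance of at least one = 1 − 0.9^K.
- K = 10: 1 expected, 65%.
- K = 20: 2 expected, 88%.
- K = 30: 3 expected, 96%.
- K = 40: 4 expected, 98.5%.

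These are chances of entering the model, not of being reported as a predictor. Fitting all 20 without a screen gives 20 × 0.05 = 1.0 null factor at P<0.05, against 0.93 with it.

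**5. Clustering in the screening tests.** Facility size is 1,000/11 = 90.9, so the design effect implies ICC = (1.2 − 1)/(90.9 − 1) = 0.0022.
- Facility-level factor: false-pass rate = 2 × (1 − Φ(1.645/√1.2)) = 13.3%; simulated (11 × 91, 1,500 runs) 13.6-13.8%.
- Individual-level factor: simulated 10-11%, against the nominal 10%.
- Assumed larger outcome ICCs of 0.02 and 0.05, facility-level factor: 32% and 48% by formula, 31% and 42-43% simulated.
- Individual-level factor with an assumed ICC of 0.2, outcome ICC 0.05: 16-18%.

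**The case against.** A reader might infer that the final models' intervals are too narrow because facility is ignored. The article does not support that: the final models have random effects, so the optimism comes from selection. Nor does clustering much distort the screen. The factors concerned are mainly measured on individuals, and at the article's own design effect the false-pass rate barely moves. Large inflation needs ICCs many times 0.0022, which are assumptions, and mostly facility-level factors, which the paragraph never names.

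A reader might also infer that the screen is the only way into the model. It is not: age, gender, education and baseline severity are named from prior literature. That answers part of the worry about baseline severity, although wording that only undertakes to consider it leaves the decision open after the data are seen.

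Third, the 88% in step 4 might be read as the chance of reporting a false predictor, or the screen as multiplying false predictors. Neither follows, since the expected count at P<0.05 is about the same with or without the screen (0.93 v 1.0).

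Finally, these are secondary analyses in a pilot evaluation. The primary remission comparison and the comparisons of mean scores do not use the screen, and the article does not say that it feeds the machine-learning models. All of this stands and limits the point. It does not defend the rule itself, which is stated outright and so is not a detail left to an analysis plan.

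**Conclusion.** The point holds as one about selection. Followed as written, the P<0.1 rule gives retained null factors about a 50% chance of P<0.05 and intervals that cover the truth about half the time. It drops or exaggerates weak true effects, and it can lose masked confounders. The 50% follows from the threshold alone when the screening and model statistics nearly coincide; where they diverge, coverage was 75% in the case simulated. The counts of passing factors rest on the assumed 10 to 40 candidates, and the weak-effect result on the chosen log odds ratio of 0.10.

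Ignoring facility in the screen is an inconsistency with the model that it feeds, but a minor one at the article's design effect. The primary remission comparison is unaffected. The rule is worth changing because it is fixed in the text and a better one needs no new data.

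**What to change.** - Remove the P<0.1 screen.
- Include baseline SRQ-20 (as a continuous score), age, gender and education in every model.
- Prespecify the social and psychological factors from the instruments listed with Fig 2 and Table 1, and fit them together in the random effects logistic model. Report all of them, whatever their P values.
- If an outcome has too few events for the list, use a penalised model. Relapse is the likeliest case, since it presupposes an earlier remission. Ordinary 95% intervals do not carry over directly to penalised estimates, so the text should say how uncertainty will be shown.
- Present single-factor results as descriptive only.

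With all candidates prespecified and no selection, each null factor has the nominal 5% error rate and 95% coverage. About 1 in 20 null factors will still reach P<0.05, which readers can judge when the full list is shown.

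The cost is a change of analysis wording. The candidate list must be fixed before outcome data are seen, and intervals will be somewhat wider.

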### Development of Predictive models for treatment response

Machine learning approaches will be used develop predictive models for treatment response to the 4 different steps of the Ebola+D mental health intervention using demographic, social, psychological and biological (proteins, mRA, genetic) variables that will be collected as part of this research project. We will use supervised machine learning (ML) classification algorithms to fit predictive models among the at-risk group of individuals for the outcome. These models will include Naïve Bayes (NB), Random forests (RF), logistic regression (LR), support vector machines (SVM), extreme gradient boosting (XGBOOST), K-nearest neighbours (KNN) and decision trees (DT). For each model, the model’s performance will then be evaluated using various performance metrics including area under the receiver operating characteristic (ROC) 11curve (AU-ROC), positive predictive value, negative predictive value, specificity, accuracy, precision, recall, and the F1-score. We will use 70% of the available data to train the models and the remaining 30% will be used in the test set. These analyses will be completed using STATA 18 and Python 13.9.2 software versions.

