### The Ebola ±D mental health intervention will involve 4 steps

Step 1 (Initiation of treatment): Patients with SRQ-20 scores of ≥6) (demonstrated 84% sensitivity and 93% specificity) [29] are advised about their scores and offered Psychoeducation (undertaken by a lay health worker, member of the VHT).

Step 2: (Management of moderate to severe cases): Patients who remain symptomatic at follow up (SRQ-20 score ≥6, after 4 weeks) despite Step 1. These will be offered Problem Solving Therapy (PST; minimum 4 sessions, maximum 8 sessions) (undertaken by a lay health worker, member of the VHT).

Step 3: (Monitoring outcomes): If after 6 sessions of PST, SRQ-20 scores are still 6 and above, complete PST sessions and add Selective Serotonin Re-Uptake Inhibitor (SSRI; such as Fluoxetine 20 mg/day for 6 months) (SSRI medication initiated by clinician).

Step 4: (Referral to Mental Health Specialist/ Clinician in charge of facility): If despite Step 3 there is no improvement (SRQ-20 scores 6 and above); or at initiation of treatment or during any phase of treatment, if someone is deemed to have a high suicide risk confirmed by the supervisor (contact general nurse or clinician), following a positive SRQ-20 item 16 (‘do you feel that you are a worthless person?’) or/and item 17 (‘has the thought of ending your life been in your mind?’) [29], then continue all existing treatment and refer to a specialised mental health worker (psychiatrist, psychiatric nurse or psychiatric clinical officer at Mubende Regional Referral Hospital).

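### The step-by-step models of treatment response lack a step-entry SRQ-20 reference and, with everyone treated, can only be prognostic

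*Protocol article*

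**What the plan says.** The section *Development of Predictive models for treatment response* states: "Machine learning approaches will be used develop predictive models for treatment response to the 4 different steps of the Ebola+D mental health intervention". The models are built "using demographic, social, psychological and biological (proteins, mRA, genetic) variables". Seven classification algorithms are listed, logistic regression among them. On validation it says: "We will use 70% of the available data to train the models and the remaining 30% will be used in the test set". Each model is to be "evaluated using various performance metrics including area under the receiver operating characteristic (ROC) 11curve (AU-ROC), positive predictive value", followed by negative predictive value, specificity, accuracy, precision, recall and F1. The section does not define response, does not name a reference model, and does not mention an untreated comparison.

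The cut-off is fixed elsewhere:
- **Entry.** The eligibility criteria (*Participants and procedure*, part 3) require an SRQ-20 score of 6 or more.
- **Primary outcome.** *Sample size and power calculations* defines remission as SRQ-20 below 6 and compares prevalence before and after in one treated group.
- **Clinical remission.** Part 3 also has a stricter version: therapy completed, and a score below 6 on two occasions a month apart.
- **Movement between steps.** The section on the four steps uses the same threshold. Step 2, for example, is for "Patients who remain symptomatic at follow up (SRQ-20 score ≥6, after 4 weeks) despite Step 1".

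For the random effects logistic models of remission, relapse and recovery (*Data collection, management, and analyses*, part iii), the factors to consider include "gender, education level, age, and baseline severity of the condition". The prediction section gives baseline severity no such role.

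**The concern.** Selection and outcome use the same threshold on the same scale, and nobody goes untreated. Part of any later fall below 6 is therefore ordinary fluctuation and regression to the mean, and it is most likely in those who started closest to 6. A classifier that picks up starting severity, directly or through variables related to it, will discriminate better than chance even if the step does nothing.

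The named metrics do not reveal this. AU-ROC has a chance value of 0.5, but starting severity alone moves it above 0.5. Accuracy, predictive values and F1 depend on the base rate. Following the section as written could lead to a statement that certain psychological, social or biological variables predict response to a step, when the data show only that they track severity at entry. What is at stake is the claim these models can carry, not the size of the before/after effect.

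**Working it through.** The article gives no performance figure for the prediction models, so there is none to reproduce. Its 94.5% power belongs to the before/after test and is not used here.

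**Inputs from the article.** Entry at SRQ-20 of 6 or more; remission below 6; 1,000 participants; 15% attrition; 30% test set.

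**Inputs assumed, because the article does not give them.** Population SD 4.5; population mean 4, 6 or 8; correlation r between baseline and follow-up of 0.2 to 0.8; zero treatment effect (same distribution at both times).

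**Step 1, model.** Score = mean + 4.5z, rounded and limited to 0–20, where z at baseline and z at follow-up are standard normal with correlation r. 400,000 people were simulated per setting, keeping those with baseline of 6 or more. Outcome: follow-up below 6. The only predictor is baseline SRQ-20, so AU-ROC = P(remitter's baseline < non-remitter's baseline) + ½P(tie).

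**Step 2, result with no treatment effect.**

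| r | AU-ROC, mean 4 | mean 6 | mean 8 | Share falling below 6 |
|---|---|---|---|---|
| 0.2 | 0.55 | 0.55 | 0.57 | 26–55% |
| 0.3 | 0.57 | 0.58 | 0.60 | 24–51% |
| 0.5 | 0.63 | 0.65 | 0.67 | 20–42% |
| 0.6 | 0.66 | 0.68 | 0.71 | 18–38% |
| 0.7 | 0.69 | 0.72 | 0.76 | 15–32% |
| 0.8 | 0.74 | 0.77 | 0.81 | 12–26% |

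At r = 0 the AU-ROC is 0.50, as it should be. Under the two-occasion remission rule, the range at r 0.5 to 0.8 is about 0.65 to 0.84, so the stricter definition does not remove the effect.

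**Step 3, accuracy.** A rule that labels everyone a non-responder has accuracy 1 − share. At r 0.5 to 0.8 that is 1 − 0.42 = 58% up to 1 − 0.12 = 88%, with no predictor at all.

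**Step 4, does AU-ROC react to a treatment effect?** With mean 6, SD 4 and r = 0.6, I lowered every follow-up score by 0, 2 or 4 points. AU-ROC was 0.68, 0.69 and 0.70, while remission was about 27%, 48% and 70%. AU-ROC hardly distinguishes no effect from a large one.

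**Step 5, how often a test set would show it.** The test set is 0.30 × 1,000 = 300, or 0.30 × 850 = 255 after attrition, for a model on all participants. For illustration I counted test sets in which AU-ROC − 1.96 × SE (Hanley–McNeil) exceeds 0.5; the article has no such rule.
- n = 300: about 31–39% at r = 0.2, 60–71% at r = 0.3, and 97–100% at r 0.5 to 0.8.
- n = 75 (assumed, for a later step): about half at r = 0.5.
- n = 30 (assumed): about a quarter at r = 0.5.

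**Step 6, a marker that only tracks severity.** A marker correlated 0.5 with baseline SRQ-20, and otherwise unrelated to outcome, reaches an AU-ROC of about 0.54 to 0.61 at r 0.5 to 0.8.

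**The case against.** The strongest reply is that this is omitted detail. A journal article need not name a benchmark for a secondary machine-learning analysis, and an analysis plan may supply one. Several parts of that reply stand:
- The metric list is introduced by *including*, so it cannot be said that the models are judged only by those measures.
- Response is not defined in the section. A score below 6 at one visit is an inference, and the article also has the two-occasion definition.
- Baseline SRQ-20 is not named as a predictor, although it is collected at baseline and would naturally count as a psychological variable.
- No decision rule about AU-ROC exceeding 0.5 is stated.

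A reader might infer that an apparently successful model is almost certain even if treatment does nothing. The documents do not support that: they give no retest correlation, and by the step rules the later steps contain only patients still symptomatic or referred, so their test sets will be below 300. At low correlation or small numbers the signal is often missed. A reader might also infer that biological markers would be falsely reported, or that the models would be used to assign patients to steps. A severity-tracking marker reaches only modest discrimination, and no section plans such use; triage rests on SRQ-20 and suicide risk.

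What does not stand is that nothing is fixed badly. The section promises models of response to treatment, by step, and a design with no untreated patients cannot deliver that whatever metrics are added later.

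**Conclusion.** The point holds in limited form. Because all participants are treated and entry and remission share one cut-off, step-entry SRQ-20 predicts the outcome with zero treatment effect whenever scores correlate over time. No named metric is set against that.

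Under the assumed inputs, the baseline-only AU-ROC is about 0.55 to 0.60 at retest correlation 0.2 to 0.3, and 0.63 to 0.81 at 0.5 to 0.8. The direction follows from the design; the size rests on an SRQ-20 distribution and correlation that the article does not give.

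The root cause is the absence of an untreated group. A severity reference would show what the other variables add to prognosis, but not who improves because of treatment. The primary outcome and the before/after comparison are unaffected, so severity is minor to moderate.

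**What to change.** In *Development of Predictive models for treatment response*:

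1. Describe the models as prognostic for outcome under each step, and say that without an untreated group they cannot identify who responds because of treatment.
2. State the outcome used for each step, for example one of the two remission definitions already in the article.
3. For each step, fit a logistic model on step-entry SRQ-20 alone as the reference. Report each algorithm's difference in AU-ROC from it, with a 95% confidence interval, on the same test data. Base any claim for psychological, social or biological predictors on that added value, and present it as prognostic rather than as evidence of a treatment effect.

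The cost is one extra simple model per step, using SRQ-20 scores already planned at baseline and monthly, plus some rewording. The downside is that the reported gain will be smaller than the raw AU-ROC suggests, and in later steps its interval may be wide.
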